**LIST OF ABBREVIATIONS AND RELEVANT DEFINITIONS**

|                |                                                                                                                                                                                                                                                                                                                                                  |
|----------------|--------------------------------------------------------------------------------------------------------------------------------------------------------------------------------------------------------------------------------------------------------------------------------------------------------------------------------------------------|
| ABR     | ABR form (General Assessment and Registration form) is the application form that is required for submission to the accredited Ethics Committee (ABR = Algemene Beoordeling en Registratie)                                                                                                                                                |
| AE      | Adverse Event                                                                                                                                                                                                                                                                                                                             |
| AR      | Adverse Reaction                                                                                                                                                                                                                                                                                                                          |
| CA      | Competent Authority                                                                                                                                                                                                                                                                                                                       |
| CCMO    | Central Committee on Research Involving Human Subjects                                                                                                                                                                                                                                                                                    |
| CV      | Curriculum Vitae                                                                                                                                                                                                                                                                                                                          |
| DSMB    | Data Safety Monitoring Board                                                                                                                                                                                                                                                                                                              |
| EU      | European Union                                                                                                                                                                                                                                                                                                                            |
| EudraCT | European drug regulatory affairs Clinical Trials GCP Good Clinical Practice                                                                                                                                                                                                                                                               |
| IB      | Investigator's Brochure                                                                                                                                                                                                                                                                                                                   |
| IC      | Informed Consent                                                                                                                                                                                                                                                                                                                          |
| IMP     | Investigational Medicinal Product                                                                                                                                                                                                                                                                                                         |
| IMPD    | Investigational Medicinal Product Dossier                                                                                                                                                                                                                                                                                                 |
| METC    | Medical research ethics committee (MREC); in Dutch: medisch ethische toetsing commissie (METC)                                                                                                                                                                                                                                            |
| (S)AE   | Serious Adverse Event                                                                                                                                                                                                                                                                                                                     |
| SPC     | Summary of Product Characteristics (in Dutch: officiële productinformatie IB1-tekst)                                                                                                                                                                                                                                                      |
| Sponsor | The sponsor is the party that commissions the organisation or performance of the research, for example a pharmaceutical company, academic hospital, scientific organisation or investigator. A party that provides funding for a study but does not commission it is not regarded as the sponsor, but referred to as a subsidising party. |
| SUSAR   | Suspected Unexpected Serious Adverse Reaction                                                                                                                                                                                                                                                                                             |
| Wbp     | Personal Data Protection Act (in Dutch: Wet Bescherming Persoonsgegevens)                                                                                                                                                                                                                                                                 |
| WMO     | Medical Research Involving Human Subjects Act (Wet Medisch-wetenschappelijk Onderzoek met Mensen)                                                                                                                                                                                                                                         |

## SUMMARY

**Rationale:** Probiotics, if instituted early in life, can give a significant reduction of development of eczema in infants at high risk of atopic diseases. In 2004 a randomized controlled trial started to investigate whether probiotics have a significant effect on the development of atopic symptoms as eczema, allergic rhinitis, food allergy and asthma. This study population has been followed until the age of two years. The present study is meant as a prolongation of the former study, we will perform a follow-up study of the included children on development of atopic diseases, in particular asthma and allergic rhinitis.

**Objective:** To establish the effect of perinatal probiotics on the prevalence of allergic disease at the age of 5 years.

**Study design:** Prospective, single blind, randomised, placebo-controlled trial.

**Study population:** Subjects are 98 predominantly Caucasian high risk children, having either a mother, or both a father and at least one sibling with past or present atopic diseases, to whom probiotics or placebo was administered perinatally during the previously carried out PANDA study.

**Intervention (if applicable):** None.

**Main study parameters/endpoints:** Development of allergic symptoms, evaluated by questionnaire and physical examination. Development of allergic asthma and allergic rhinitis, measured by lung function testing, nitric oxide measurements in exhaled air, and specific IgE to allergens.

**Nature and extent of the burden and risks associated with participation, benefit and group relatedness:** Parents and child are asked to fill in a questionnaire, and pay one visit to the out patient department for physical examination, blood sampling and pulmonary function testing with measurement of exhaled nitric oxide. The risks of these procedures are negligible and the burden minimal. It should be carried out specifically in these children, since they have been included in the former study and received placebo or probiotics.

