## **2. STUDY DESIGN**

A randomised double-blind placebo-controlled prospective study was carried out in 156 high-risk children. 98 children completed the intervention period and the two years of follow-up. The present study comprises a follow-up at the age of 5 or 6 years, in the outpatient clinic.

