### 3. STUDY POPULATION

- 3.1 **Population (base):** Children who previously participated in the PANDA study
- 3.2 **Inclusion criteria:** Children who previously participated in the PANDA study
- 3.3 **Exclusion criteria:** None
- 3.4 **Sample size calculation:** We will try to get as little as possible loss to follow-up by trying to find all the former participants of the PANDA-study and to ask for the collaboration.

For the pilot study evaluating the diagnostic value of measurement of nasal nitric oxide, we will evaluate the complete cohort, not considering whether the child has received probiotics. We estimate the prevalence of allergic rhinitis to be 15% in this cohort. To be able to detect a statistical significant difference between nasal NO in the subjects with a diagnosis of allergic rhinitis from the questionnaire and subjects who do not, we will need a minimum of 10-15 participants with allergic rhinitis, and the same amount who do not suffer from allergic rhinitis. In evaluating this, we consider the means for NO in both groups to be 450 and 600 ppb, the standard deviation 115 ppb, the power 90% and the alfa 0.05. With the expected prevalence of allergic rhinitis (14 of 95 participants), this should be possible.

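### The Summary gives the study population as 98 children, the number who completed PANDA, while section 3 admits every participant of the 156-child trial; the plan does not say which governs

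*Protocol*

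**What the plan says.** Section numbers here are those in the body of the protocol, which run one lower than in the table of contents.

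- **Summary, study population:** "Subjects are 98 predominantly Caucasian high risk children". Completion is not mentioned.
- **Section 2:** "A randomised double-blind placebo-controlled prospective study was carried out in 156 high-risk children", followed by "98 children completed the intervention period and the two years of follow-up". This is the only place that explains where 98 comes from.
- **Sections 3.1 and 3.2:** population base and inclusion are both "Children who previously participated in the PANDA study". Section 3.3 reads "Exclusion criteria: None".
- **Section 3.4:** loss to follow-up is to be kept small by "trying to find all the former participants of the PANDA-study". For the nasal nitric oxide pilot, which is to use the whole cohort regardless of allocation, it adds: "We estimate the prevalence of allergic rhinitis to be 15% in this cohort" and "With the expected prevalence of allergic rhinitis (14 of 95 participants), this should be possible".
- **Section 8.1:** relative risks with 95% confidence intervals are planned for the main endpoint. The Summary calls the follow-up study randomised and placebo-controlled.

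Nothing in the protocol reconciles 98, 95 and all former participants.

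**The concern.** The 98 are defined by what happened after randomisation: finishing the intervention and two years of follow-up. Stopping PANDA could depend on the arm and on early atopic symptoms, and those symptoms could in turn be related to asthma or rhinitis at 5 or 6 years. A relative risk confined to completers is then no longer protected by randomisation, although it would be reported under a randomised label.

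The ambiguity has practical force. One team could approach 98 families and another 156, and each could point to text that supports it. The choice is made at recruitment. A later analysis plan cannot restore families who were never contacted, so this point cannot be left to a statistical analysis plan.

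**Working it through.** **Inputs from the protocol:** 156 children in the trial and 98 completers (section 2); 98 subjects (Summary); 95 participants, 14 expected with rhinitis, prevalence 15% (section 3.4).

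**1. The plan's own figure.** 0.15 × 95 = 14.25, which agrees with the stated 14. The same prevalence gives 0.15 × 98 = 14.7 and 0.15 × 156 = 23.4.

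**2. Which base does 95 fit?** 95/98 = 96.9%; 95/156 = 60.9%. Section 3.4 aims at minimal loss and states no attrition rate, so 95 sits more naturally with 98. It is still compatible with 61% attendance out of 156.

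**3. Children left out if 98 governs.** 156 − 98 = 58, and 58/156 = 37.2%.

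**4. How far a completer result could differ from the full result.** The protocol gives no arm sizes, no dropout by arm and no outcomes. The following are assumptions for illustration: equal arms of 78, each with 49 completers and 29 non-completers.

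*No difference among completers.* Take 15% in both arms among completers (RR 1.00), and 10% (probiotic) against 20% (placebo) among non-completers.

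RR in all 156 = (0.15 × 49 + 0.10 × 29) / (0.15 × 49 + 0.20 × 29) = 10.25/13.15 = 0.78. With the non-completer rates reversed, 13.15/10.25 = 1.28.

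*No difference in the full trial.* Take 15% in both arms overall. With missing share m = 58/156, the completer prevalence in an arm is (0.15 − m × prevalence in the missing)/(1 − m).

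| Prevalence in non-completers, probiotic / placebo | Completer prevalence, probiotic / placebo | Completer RR |
|---|---|---|
| 15% / 15% | 15.0% / 15.0% | 1.00 |
| 10% / 20% | 18.0% / 12.0% | 1.49 |
| 5% / 25% | 20.9% / 9.1% | 2.30 |

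Bias appears only if non-completers differ by arm, and its direction follows the assumption.

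**5. Precision.** At 15% in both arms, SE(log RR) = √[2(1 − 0.15)/(0.15 n)].

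- n = 49 per arm: SE = √(1.7/7.35) = 0.481; 95% CI around RR 1 is 0.39 to 2.57.
- n = 78 per arm: SE = √(1.7/11.7) = 0.381; 95% CI is 0.47 to 2.11.

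The second interval assumes that all 58 are recovered, so it is a best case.

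**The case against.** The strongest reply is that the operative text already admits everyone. Sections 3.1 to 3.4 do so, section 9.2 recruits among the participants of the previous study, and the Introduction describes a follow-up of the children previously included. The Summary's own rationale also speaks of the included children. Against these stands one descriptive number in a synopsis, and section 2 only reports history. This stands: if section 3 governs, exclusion of non-completers is not part of the design.

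A reader might infer from the 95 that completers are the real working population. The protocol does not show that. The number appears only in the pilot calculation, which ignores allocation, and it also fits 156 with attrition. A reader might also infer that the randomised comparison is already broken. That is not supported either: the loss is conditional on the 98 governing, and no bias is demonstrated. The risks among non-completers used above are assumed, not documented.

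Two smaller points also stand. Section 2 says that the trial was carried out in 156 children, so 156 randomised is the natural reading but not the literal one. The protocol also does not say whether the 58 can still be reached.

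None of this removes the conflict. A Summary that counts only as many subjects as there were completers, beside an inclusion rule that admits all, leaves open who is approached.

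**Conclusion.** The inconsistency between the Summary and section 3 is certain. Its consequence is conditional. If the 98 governs, 37% of the children are left out on post-randomisation grounds and the main relative risk loses its intention-to-treat protection. The size and direction of any bias cannot be derived from the protocol. The relative risks of 0.78 and 1.28, and of 1.49 and 2.30, show what assumed differences by arm among non-completers would do; they are not estimates. They rest on equal arms, equal dropout by arm and 156 being the number randomised.

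Parents' knowledge of allocation when they decide on participation (section 6.2) is a separate issue. It affects a cohort of 98 or of 156 alike, and settling the denominator does not cure it.

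**What to change.** Before recruitment, replace the number in the Summary with a statement that matches section 3, for example:

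*All 156 children of the PANDA trial are approached, whether or not they completed the intervention or the two-year follow-up, and are analysed in the arm to which they were randomised.*

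Then:

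- Report participation by arm, with 156 as the denominator.
- Keep the completers as a sensitivity analysis.
- State which base the 95 in section 3.4 is drawn from.
- If participation weights are used, build them on PANDA baseline data only. Two-year data will be largely missing for the 58, who by definition did not complete both the intervention and the two-year follow-up.

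The sensitivity analysis and any weighting may sit in a statistical analysis plan. The statement of who is approached belongs in the protocol.

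**Cost:** a wording change, and letters and calls to up to 58 more families, which section 3.4 already promises. Some families will give only a questionnaire or a physician's report. Their children can be classified for rhinitis, but not for asthma as section 6.1.1 defines it, because that definition requires FEV1 reversibility or raised exhaled NO in addition to symptoms. The gain in numbers will therefore be smaller for asthma than for rhinitis.

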## INTRODUCTION AND RATIONALE

The last decennia a rising incidence of allergy and atopic disorders is seen, especially amongst children. The aim of this study is to investigate possible primary prevention in high risk children by means of administration of probiotics from 4-6 weeks prenatally until the age of one year.

The hypothesis is, that early administration of probiotics to pregnant women with allergy and subsequently to their offspring, leads to prevention or reduction of development of sensitisation and allergic disorders in childhood.

Modification of the intestinal flora early in life by administration of probiotic bacteria may be a potential approach to prevent atopic disease. Strachan (1) suggested a decreased occurrence of T helper type 1 (Th1)-associated infections to be a causative factor in the increased prevalence of allergy. More recently, modifications of the hygiene hypothesis have moved away from the impact of Th1-driving infections and towards the influence of the diversity of the microbial exposure in general during establishment of the intestinal flora (2,3). In industrial countries having a high degree of hygiene, changed microbial exposure might cause an altered composition of the intestinal flora and thus, an altering of the immunomodulatory microbial signalling posed during the critical stages of immune development in infancy (4). Atopic disease is the result of a T helper type 2 (Th2)-deviated immune response characterized by the production of the cytokines IL-4, IL-5, and IL-13. According to the hygiene hypothesis, insufficient infection-related Th1 responses during the neonatal period and infancy were considered to lead to unrestricted Th2 responses, resulting in allergic diseases.

Because the gastro-intestinal (GI) tract encompasses the largest surface of the human body where microbial products interact with the immune system, much attention is focused on the possibility that the intestinal flora may play a role in the development of atopic disease (2). Indeed, different bacterial colonization patterns have been observed in the intestinal flora of allergic children when compared with non-allergic children. Lactobacilli and bifidobacteria are more commonly found in the intestinal flora of non-allergic children, while allergic children seem to harbour higher number of clostridia and staphylococci (5,6). Lactobacilli and bifidobacteria are most frequently investigated probiotic species for possible beneficial effects in prevention and treatment of allergic disease (7). Preliminary data indicate that probiotic bacteria can be effective in prevention and treatment of atopic disease (8-13). Perinatal administration of probiotic bacteria (*Lactobacillus rhamnosus* GG) significantly reduced the development of eczema during the first 2-4 years of life in children with a family history of atopic disease (8,9). In addition, specific probiotic strains have been beneficial in the treatment of infants suffering from atopic eczema and cow's milk allergy by significantly decreasing the SCORAD score (10,11,14). The mechanism by which probiotic bacteria may modify immune-mediated diseases such as atopic disease, and which different species or strains may contribute are poorly understood.

[name] et al(15,16) showed the ability of live lactic acid bacteria to modulate the immune responses by inducing IL-10 in peripheral blood mononuclear cells, and these effects appeared to be strain specific. Based on this study, they selected *B. Bifidum*, *B. infantis*, and *Lc Lactis* (because of their good IL-10-inducing capacity as well as efficient inhibition of IL-5 and IL-13) to be used as a multi-species probiotics in a clinical trial on primary prevention of allergic diseases by probiotic bacteria. *B. Bifidum* was most potent to polarize dendritic cells to drive Th1 cell responses involving increased IFN-gamma producing T cells concomitant with reduction of IL-4-producing T cells. *L. Lactis* was much less effective in this respect.

This study will encompass a follow-up of the previously included children in the above mentioned double blinded randomized clinical trial performed by [name] from 2003 till 2007. It will be carried out when the children have reached the age of 5 years. Since [name] completed follow-up till the age of 2 years, a thorough evaluation of the development of asthma and allergic rhinitis was not possible. The diagnosis of asthma is best made at an age beyond 5 years for reasons of lung function testing, and the prevalence of allergic rhinitis rises from the age of 4. The aim of this follow-up study is to study if administration of probiotics during pregnancy and in the first year of life has any influence on the prevalence of asthma and allergic rhinitis, in Caucasian children at high risk of developing atopy, at the age of 5 or 6 years.

Besides this, we wish to perform a pilot study evaluating the diagnostic value of measurement of nasal nitric oxide (nNO) in the diagnosis of allergic rhinitis. An effect of allergic rhinitis on nNO is not consistently reported. However, most studies suggest that nNO is increased in allergic rhinitis. Normal values for nNO in children are well defined by Struben et al. De Winter et al will shortly publish an evaluation of methodology for nNO-measurements, with good reproducibility and applicability, investigated at the Department of Paediatric Pulmonology of our hospital. We do not expect a direct relationship between probiotics and nNO, but want to support the diagnosis of allergic rhinitis. This test is easily available in our hospital, easy to perform and not experienced as invasive by the child. As we expect a direct relationship between the severity of allergic rhinitis and level of nNO, we wish to evaluate the predictive value of the measurement of nNO for the diagnosis of allergic rhinitis.

